### 3.6 Endpoints of the Study

#### Primary endpoints:

- ✓ PFS and OS, per RECIST version 1.1 assessed by IRC.

#### Secondary endpoints:

- ✓ PFS per RECIST version 1.1 and iRECIST, ORR, DCR, DOR, 6-month PFS rate, 12-month PFS rate, 12-month OS rate, 18-month OS rate, and QOL assessed by investigators.
- ✓ Safety and tolerability based on incidence and severity of AEs and SAEs, as well as abnormal laboratory test indicators.

### 4. Study Design

This is a multicenter, randomized, double-blind, parallel-controlled phase III clinical trial.

#### 4.1 Sample Size Calculation

##### 4.1.1 Method of Sample Size Calculation

There are 3 arms in this study: Intervention arm 1 (TQB2450, Anlotinib, Carboplatin, and Etoposide); Intervention arm 2 (TQB2450 placebo, Anlotinib, Carboplatin, and Etoposide); Control arm (TQB2450 placebo, Anlotinib placebo, Carboplatin, and Etoposide). The primary efficacy endpoints of this trial are PFS and OS. In this study, a fixed-sequence test will be used for comparisons between treatment groups.

The safety analysis and re-estimation of sample size will be conducted by the Independent Data Monitoring Committee (iDMC). The re-estimation of sample size based on PFS is planned after 50% of the planned PFS events (174 cases). At the same time, a safety analysis will be performed. The interim analysis will be conducted by iDMC. One interim analysis for OS is planned for this study after 70% of the planned OS events. If expected efficacy is observed, early declaration of the study due to efficacy would be considered. The interim analysis will be conducted by iDMC.

The previous study showed that the median OS and PFS in the control arm were 10 and 4 months, respectively [5]. Patients were enrolled within a 12-month accrual period with an 18-month follow-up and were randomly assigned (1:1:1) to three groups. The power was 85% with a type I error rate of 0.050 and a dropout incidence of 10%. The type I error rate in the interim analysis for PFS will be controlled by the Method Based on the Sum of P-values (MSP). The initial sample size in this study will be estimated based on PFS using a computer simulation program.

##### 4.1.2 Sample Size Estimation in the Intervention Arm 1

Assuming that the HR for PFS in the intervention arm 1 compared with the control arm is 0.6, the hazard rate in the intervention arm 1 is 0.1040, and that in the control arm is 0.1733 along with exponential distribution. Approximately 165 PFS events are expected if 174 patients are enrolled. A total of 194 patients are recruited and randomly assigned (1:1) to intervention arm 1 and control arm, considering an approximate dropout incidence of 10%. The interim analysis will be conducted when the planned PFS events are ~83. The final analysis will be performed after ~165 of the planned

PFS events.

Assuming that the HR for OS in intervention arm 1 compared with the control arm is 0.7, 284 OS events are expected with the type I error rate of 0.050 if 381 patients are enrolled. A total of 424 patients were recruited and randomly assigned (1:1) to intervention arm 1 and control arm, considering an approximate dropout incidence of 10%.

#### **4.1.3 Sample Size Estimation in the Intervention Arm 2**

Assuming that the HR for PFS in the intervention arm 2 compared with the control arm is 0.65, the hazard rate in the intervention arm 2 is 0.1126, and that in the control arm is 0.1733 along with exponential distribution. Approximately 231 PFS events are expected if 242 patients are enrolled. A total of 270 patients are recruited and randomly assigned (1:1) to intervention arm 2 and control arm, considering an approximate dropout incidence of 10%. The interim analysis will be conducted when the planned PFS events are ~116. The final analysis will be performed after ~231 of the planned PFS events.

Assuming that the HR for OS in intervention arm 2 compared with the control arm is 0.72, 331 OS events are expected with the type I error rate of 0.050 if 442 patients are enrolled. A total of 492 patients were recruited and randomly assigned (1:1) to intervention arm 2 and control arm, considering an approximate dropout incidence of 10%.

#### **4.1.4 Determination of Total Sample Size**

Considering the sample size estimation in sections 4.1.2 and 4.1.3, 738 subjects will be finally enrolled in this trial and be randomly assigned (1:1:1) to three groups. The interim analysis and final analysis for PFS are conducted for this trial after 174 and 347 cases of the planned PFS events, respectively. The interim analysis and final analysis for OS are performed for this trial following 348 and 497 cases of the planned OS events, respectively.

#### **4.2 Interim Analysis**

The interim analysis will be conducted by iDMC to assess the risk-benefit in the phase III trial. The iDMC, consisting of two independent oncologists and one independent statistician, is independent of the sponsors and investigators.

The analysis of safety and efficacy and re-estimation of sample size will be performed by iDMC in this trial. The re-estimation of sample size is mainly based on PFS and is planned after 50% of the planned PFS events (174 cases). At the same time, a safety analysis will be performed. If the planned sample size cannot achieve adequate power in the final analysis, the sample size will be increased. In contrast, if obtained power is adequate, the sample size will not be changed. The determinations for sample size are detailed in the iDMC guidelines. In parallel, efficacy analysis for OS is planned in this study after 70% of the planned OS events. If expected efficacy is observed, early declaration of the study due to efficacy would be considered. The interim analysis for OS and the final analysis for PFS will be carried out at the same time, whichever comes later.

Based on the analysis results, IDMC will provide a written recommendation to the sponsor on whether to carry out the trial or to continue the trial after modifying the protocol. The sponsor will make the appropriate decisions on the research project based on IDMC's recommendations, such as

termination of the trial due to safety or lack of efficacy.

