#### (2) Type I error control for the re-estimation of sample size based on PFS

The safety analysis, re-estimation of sample size, and efficacy analysis will be conducted by the iDMC. The re-estimation of sample size based on PFS is planned after 50% of the planned PFS events (174 cases). At the same time, a safety analysis will be performed. The interim analysis will be conducted by iDMC.

The non-blind re-estimation of sample size is a procedure with multiple tests, with a concern on data dependency in different stages, which would increase the inflation of the type I error rate. To address this problem, P values in two stages will be combined using the MSP.

According to the preliminary test, in the PFS interim analysis based on the re-estimation of sample size, the one-side significance level is set as  $\alpha_1=0.005$ , and the futility boundary is set as  $b_1=0.45$  in the first stage; the one-side significance level is set as  $\alpha_2=0.2050$  in the secondary stage. No early discontinuation of the study due to PFS efficacy would be considered.

- Either  $P_1 \leq \alpha_1$  or  $P_1 > \alpha_1$ , once  $P_1 \leq b_1$ , the trial will continue to the second stage, without early discontinuation due to PFS efficacy;

- If  $P_1 > b_1$ , the trial will terminate early for futility;
- If the trial could proceed into the second stage,  $P_1 + P_2 \leq \alpha_2$  [that is, adjust P value =  $\alpha_1 + (P_1 + P_2)(b_1 - \alpha_1) - 1/2 (b_1^2 - \alpha_1^2) \leq 0.025$ ], the between-group difference in PFS will be considered as statistically significant.

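### The final PFS analysis will come at about 550 events, not 347, because it waits for the OS interim; the 50% interim fraction and the 85% PFS power do not describe that analysis

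*Protocol*

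**What the plan says.** Protocol section 4.1.4 fixes the PFS counts for the three arms together: "The interim analysis and final analysis for PFS are conducted for this trial after 174 and 347 cases of the planned PFS events, respectively". The same section sets the OS interim at 348 deaths and the final OS analysis at 497.

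Section 13.2.2 (2) describes the early look as half-way: "The re-estimation of sample size based on PFS is planned after 50% of the planned PFS events (174 cases". Sections 4.1.1 and 4.2 say the same.

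Section 4.2 then couples the two endpoints: "The interim analysis for OS and the final analysis for PFS will be carried out at the same time, whichever comes later". The same section provides that the sample size is raised if the planned size would not give adequate power at the final analysis. It leaves the rule itself to the iDMC guidelines.

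The protocol nowhere gives the number of PFS events expected at the joint analysis.

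**The concern.** Progression comes much sooner than death in this disease, so 347 PFS events and 348 deaths cannot fall close together in time. If the later trigger governs, the PFS analysis is always held back until the deaths accumulate, and 347 is then not the count at which PFS will be tested. Three stated design figures depend on it: the final event count, the 50% fraction at the interim, and the 85% power for PFS.

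The figures also feed a decision. The unblinded re-estimation compares expected power with what is adequate at the final analysis, and 347 is the only final PFS count in the document. A power projection to 347 and one to the joint analysis can lead to different recommendations on enrolment.

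**Working it through.** **Inputs (sections 4.1.1 to 4.1.4).** Control medians: "The previous study showed that the median OS and PFS in the control arm were 10 and 4 months, respectively". Timing: "Patients were enrolled within a 12-month accrual period with an 18-month follow-up and were randomly assigned (1:1:1) to three groups". PFS hazard ratios are 0.60 (arm 1) and 0.65 (arm 2). OS hazard ratios are 0.70 and 0.72. There are 738 patients, 246 per arm. Survival is taken as exponential and accrual as uniform over 12 months.

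**Monthly hazards.** PFS: ln2/4 = 0.1733 for control, 0.1040 for arm 1, 0.1126 for arm 2 (all as stated). OS: ln2/10 = 0.0693, then 0.0485 and 0.0499.

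**Formula.** Expected events in an arm of n patients with hazard λ at calendar month T:
- T ≤ 12: (n/12)·[T − (1 − e^(−λT))/λ]
- T > 12: n·{1 − [e^(−λ(T−12)) − e^(−λT)]/(12λ)}

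**Reproducing the plan.** At month 30 (12 + 18) the formula gives:
- PFS: 164.7 events in 174 patients (stated 165) and 231.0 in 242 (stated 231)
- OS: 283.6 in 381 (stated 284) and 331.2 in 442 (stated 331)

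The three-arm totals follow: 1.5 × 231 = 346.5, so 347; 347/2 = 173.5, so 174; 1.5 × 331 = 496.5, so 497; 0.7 × 497 = 347.9, so 348; 1.5 × 492 = 738. The model is therefore the plan's own.

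**When each trigger is met (738 patients, no dropout).**

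| Trigger | Month | PFS events | Arm 1 + control | Arm 2 + control | Deaths |
|---|---|---|---|---|---|
| 174 PFS events | 7.7 | 174 | 121 | 124 | 89 |
| 347 PFS events | 11.7 | 347 | 240 | 245 | 192 |
| 348 deaths | 17.8 | 554 | 378 | 385 | 348 |

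The deaths are the later trigger by about six months. Interim fraction: 174/554 = 31%.

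**Sensitivity (assumed values).**
- 10% lost per 30, 12 or 6 months: 552, 550 or 544 PFS events at 348 deaths
- Accrual of 9 to 30 months in place of 12, with the same dropout range: 510 to 558
- 664 evaluable patients: 533
- No effect on either endpoint: 572
- No OS effect but the planned PFS effect: 496

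The fraction stays between 174/572 = 30% and 174/496 = 35%.

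**Power of the MSP test.** Take Z1 ~ N(√(d1/4)·|ln HR|, 1) and an independent Z2 ~ N(√((d2 − d1)/4)·|ln HR|, 1), with one-sided P values P1 and P2. Reject if P1 ≤ 0.45 and P1 + P2 ≤ 0.2050, without early rejection for efficacy, as section 13.2.2 (2) states. The planned pairwise counts give 84.6% (83 of 165 events, HR 0.60) and 84.5% (116 of 231, HR 0.65), which matches the stated 85%. With 738 patients:

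| Comparison | True HR | Power at 347 total events | Power at joint analysis |
|---|---|---|---|
| Arm 1 v control | 0.60 | 95% (121 of 240) | 98% (121 of 378) |
| Arm 2 v control | 0.65 | 86% (124 of 245) | 93.5% (124 of 385) |
| Arm 2 v control | 0.66 | 84% | 92% |
| Arm 2 v control | 0.69 | 75% | 87% |
| Arm 2 v control | 0.70 | 72% | 84% |

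Under the null the one-sided rejection rate is 0.021 at either count.

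Against a target of 85%, the two projections disagree for arm 2 when the true hazard ratio is about 0.66 to 0.69. This uses unconditional power at a fixed true effect. The iDMC rule may use conditional power, which would move the band but leave the dependence on the final count.

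**The case against.** The sections do not flatly contradict each other. Taking the later of two triggers makes 347 a floor for PFS, and 174 is correctly half of the planned 347. All stated counts reproduce. This stands, and it is why the fault is a misdescribed analysis and not a wrong sum.

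Several stronger conclusions that a reader might draw do not hold:

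- **Inflated error.** The MSP limits act on stage-wise P values and do not depend on the information fraction, so the error rate does not move, and power only rises.
- **Needless enrolment as a certainty.** The iDMC guidelines are not shown and may already project to the joint date. The supplementary response tables list 246 + 245 + 247 = 738 patients, so no increase is visible.
- **A weak effect as the telling case.** At HR 0.75 for arm 2, power is 54% at 347 events and 69% at the joint analysis. Both fall short of 85%, so the choice of count changes nothing there.
- **The gap from 165 and 231 as a product of the joint timing.** Those pairwise counts are already passed at 347 total events (240 and 245), because 738 was set by OS. They are the counts needed for 85% power. Exceeding them is no error, and a report would give observed events.

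**Conclusion.** The point holds in this form: under the protocol's assumptions the final PFS analysis takes place at about 550 events (about 378 and 385 in the two comparisons with control), the re-estimation look is at about 31% of that information, and PFS power at the planned hazard ratios is about 94% to 98%. Part of the gain over 85% comes from the OS-driven sample size (95% and 86% already at 347 events) and the rest from the later cut.

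The count rests on exponential survival and uniform accrual, but 496 to 572 covers every variation tried, and the interim fraction stays at 30% to 35%. Error control is sound. The exposure is an unblinded re-estimation that, if it reads 347 as the final count, could recommend an increase that the real analysis does not need. That is a possibility limited to a narrow range of effects for arm 2 against control. It deserves correction because the decision concerns a primary endpoint and the text is easily put right.

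**What to change.** In sections 4.1.4 and 4.2, state that 347 is the minimum number of PFS events and that the final PFS analysis is expected at the OS interim with about 550. In sections 4.1.1, 4.2 and 13.2.2 (2), add that 174 events are about 31% of the information expected then. Restate PFS power at the joint analysis for both comparisons with control. Specify, in the protocol and the iDMC guidelines, that the re-estimation judges power at the joint-analysis count.

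The MSP limits need no change, and since the rule is a plain sum of two P values there are no stage weights to revise. The cost is a few sentences and one re-run of the sample-size simulation. The only drawback is that the stated interim fraction becomes smaller.

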### **4.3 Randomization**

This is a multicenter, randomized, double-blind, parallel-controlled phase III clinical trial. A centralized randomized procedure will be used, with each center competing for enrollment. The centralized randomization procedure will use the eRand centralized randomization system. The independent statisticians upload the blinding code after the project's official launch. For patients with signing the informed consent form and were eligible for screening, the investigators log in to the randomization system and fill in the patient information (including participating center, initials, gender, date of birth, stratification factors for subjects, etc.). After confirming the basic information and stratification factors of subjects, randomization will be conducted by the investigator or authorized personnel to obtain the random number and the corresponding drug number. The appropriate research drugs are issued by the drug administrators of each participating center. The random number of each subject is a unique and permanent identifier. For those who are successfully randomized but do not receive the research drug, their drug and drug number shall be discarded and cannot be redistributed to others. The supervisor can log in to the system to verify the patient information and the drug use of each center, and send questions to the responsible individuals for any information in doubt. Subjects must start study treatment within 3 days following randomization. To ensure the equilibrium across three groups, stratification factors are designed as follows:

- ECOG PS: 0 or 1;
- Brain metastases (yes/no);
- Liver metastases (yes/no).

### **4.4 Blind Design**

#### **4.4.1 Double-blind Review Process**

In this trial, a double-blind (double-simulation) design will be used in which the investigators, the research staff involved in the efficacy evaluation, the data managers, statisticians, and the subjects and their guardians are blinded to the grouping. The TQB2450 placebo and anlotinib hydrochloride placebo used in the control arm are manufactured, prepared, and tested by the sponsor to ensure the identification of the appearance, packaging, and smell.

#### **4.4.2 Blinding Code**

The independent statisticians irrelevant to the final analysis of the trial develop the blinding code and upload blinding code to the eRand centralized randomization system after the project's official launch. The blinding code will be saved in the eRand centralized randomization system during the trial.

#### **4.4.3 Emergency Unblinding**

##### **Conditions for emergency unblinding**

Emergency unblinding can be conducted when the subjects need to be rescued due to emergency events and the rescue operations depend on the known treatment the patient has received.

**Process for emergency unblinding**

An online emergency unblinding method will be adopted in this trial. If necessary, the primary investigator at each center can request an online emergency unblinding for a specific subject through the centralized randomization system: (1) The primary investigator at each center locates the record of the corresponding subject in the centralized randomization system; (2) Click the "emergency unblinding" and fill in the detailed reason for the emergency unblinding in the pop-up page; (3) After clicking "Confirm", the sponsor will receive an application email of emergency unblinding, and click "Agree" or "reject"; (4) If the sponsor clicks "Agree", the online emergency unblinding is successful, then the investigators will receive the emergency unblinding receipt, and the system will notify relevant personnel by email. Only the primary investigator of each center has access to emergency unblinding.

**Emergency unblinding for pharmacovigilance**

In the case of SUSAR, the independent pharmacovigil commissioners shall apply for the blinding code to the system manager. The system manager will directly send the blinding code to the pharmacovigil commissioners who shall be responsible for keeping and maintaining the blinding code.

**The record of emergency unblinding**

After successful emergency unblinding, the centralized randomization system will generate an emergency unblinding receipt. The investigators will sign the printed emergency unblinding receipt for confirmation, and the original copy will be kept in the center. The subsequent emergency unblinding shall be recorded in the corresponding original medical record/ electronic case report form (eCRF). The investigators fill in the emergency unblinding record and send the scanned copy to the sponsor for preservation.

**Handling after emergency unblinding**

Once the subject is unblinded, the subject with this number will withdraw from the trial and will not be replaced. The condition of the subject shall be followed up until the patients improve or reach a stable state.

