**Post-treatment Follow-ups**

All subjects will be followed up every 8 weeks (including telephone follow-up) to collect data on other antitumor therapy and disease status. The treatment regimens, cycles, and outcomes of any other treatment must be recorded during the trial. Post-treatment follow-up will be conducted until

death. Reasons and the date of death will be recorded for overall survival analysis.

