## 13. Statistical Analysis

### 13.1 Analysis Datasets

**Intention-to-treat (ITT) Analysis Set:** All randomized patients are included for efficacy analysis, according to the ITT principle. For the ITT population, patients will be considered in the treatment group as randomized.

ITT population is the primary analysis set and will be used for all efficacy and baseline characteristics analysis.

**Per-protocol Set (PPS):** All patients of the ITT population who receive the pre-defined minimum cycle of study treatment, had at least one imaging evaluation, without any major protocol deviation, with favorable compliance, and complete CRF.

PPS will be used for the per-protocol analysis of the primary efficacy variable and key secondary efficacy variables. The final PPS will be determined by the principal investigator, statisticians, and sponsors before the database lock.

**Safety Analysis Set (SS):** All randomized patients who receive at least one study treatment and have at least one safety assessment.

SS will be used for the safety analysis. For the SS population, patients will be considered in the treatment group as treated.

Baseline characteristics analysis will be performed for the ITT population. The analysis of the primary efficacy variable will be performed for the ITT and PPS population. The primary set for efficacy is the ITT. The analysis of laboratory data, AEs, and adverse reactions will be performed for the SS population.

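### The emergency-unblinding rule withdraws the patient from the trial, which contradicts the protocol's own PFS and OS follow-up, and the sponsor may refuse the request

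*Protocol*

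**What the plan says.** Section 4.4.3, Handling after emergency unblinding, gives two rules. On status: "the subject with this number will withdraw from the trial and will not be replaced". On follow-up, the patient's condition "shall be followed up until the patients improve or reach a stable state". Neither tumour assessment nor survival is mentioned.

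The same section sets out access. Unblinding is reserved for an emergency in which rescue depends on knowing the treatment. "Only the primary investigator of each center has access to emergency unblinding". After the request is entered, "the sponsor will receive an application email of emergency unblinding" and either agrees or rejects; the code is released only on agreement. No time limit, out-of-hours route or override is given.

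Elsewhere:
- Section 7, Post-treatment Follow-ups: "All subjects will be followed up every 8 weeks (including telephone follow-up"; this continues until death.
- Section 8, table of concomitant medications: refers to an OS follow-up section that applies after study withdrawal.
- Section 9: imaging continues every 2 cycles in patients who stop study drug for reasons other than progression. It ends at new antitumour therapy, progression, withdrawn consent or death.
- Section 13.1: "All randomized patients are included for efficacy analysis, according to the ITT principle".

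**The concern.** PFS and OS are the primary endpoints, and a patient counts fully only if progression and death dates keep being collected. Section 4.4.3 is the rule a site would open after breaking the code, and it gives a different end to follow-up from sections 7 and 9. If it is followed to the letter, endpoint follow-up stops in a small group selected by a serious emergency. Such patients plausibly have a worse prognosis, and the rate of such emergencies may differ by arm, so the censoring could be informative and could favour the arm with more toxicity.

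The access rule is a separate defect. The stated condition is that rescue depends on the allocation, yet access to it depends on a decision by the sponsor, which may be no.

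**Working it through.** **Step 1. Does withdrawal in this protocol end endpoint follow-up?**

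| Place | What it implies |
|---|---|
| 4.4.3, Handling after emergency unblinding | Leaves the trial; follow-up to improvement or stability |
| 3.2.1 | Progression and intolerable AEs count as withdrawal, but so do withdrawn consent and loss to follow-up |
| 3.2.2 | Withdrawn subjects are followed for AEs, and last examination results are carried forward; no imaging or survival follow-up required |
| 7, Post-treatment Follow-ups | All subjects, until death |
| 8, table | OS follow-up exists after study withdrawal |
| 9 | Imaging continues after stopping study drug; unblinding is not a listed stopping reason |
| 13.4.1, OS | Treatment after withdrawal is a model covariate, so OS is analysed beyond withdrawal |

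For OS, most places point to continued follow-up. For PFS the protection is weaker: section 9 speaks of patients who stop study drug, whereas 4.4.3 says the patient leaves the trial. The text does not settle which rule governs.

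**Step 2. The plan's own OS figure (arm 1 vs control).** Inputs from sections 4.1.1 and 4.1.2: HR 0.70, 85% power, two-sided alpha 0.05. Schoenfeld events = 4 × (1.960 + 1.036)² / (ln 0.70)² = 4 × 8.98 / 0.1272 ≈ 283, against 284 stated. The figure reproduces.

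**Step 3. Power if some OS events were lost.** Power = Φ(½ × √events × |ln 0.70| − 1.96).

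| Events lost | 0% | 1% | 2% | 5% | 10% |
|---|---|---|---|---|---|
| Power | 85.2% | 84.9% | 84.5% | 83.4% | 81.4% |

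Power is not the main issue.

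**Step 4. Selective loss.** The documents give no unblinding rate, so the rates are assumed. Simulation with 246 per arm (738/3), exponential OS, control median 10 months, 12-month accrual, 18-month follow-up and a base HR of 0.70. Further assumptions: unblinding falls in months 0 to 6, the hazard of death is three times higher afterwards, and under the literal reading the patient is censored 0.5 month after unblinding.

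| Unblinded, arm 1 vs control | HR, full follow-up | HR, censored | Difference |
|---|---|---|---|
| 1% vs 1% | 0.702 | 0.701 | 0.001 |
| 5% vs 1% | 0.723 | 0.701 | 0.022 |
| 5% vs 0% | 0.730 | 0.704 | 0.026 |
| 10% vs 2% | 0.746 | 0.700 | 0.046 |

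At 5% vs 0% the difference is about 0.02 if the later hazard only doubles, and nil if it does not change. At 2% vs 0% with a tripled hazard it is about 0.01. With a base HR of 1.0, the rate of falsely claiming benefit under censoring stayed below the one-sided 0.025 (0.019 at 5% vs 1%, 0.0215 at 10% vs 2%). The effect on PFS was not computed.

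**Step 5. The access rule.** Within 4.4.3, the condition for unblinding is an emergency rescue that depends on the treatment, while the process makes release conditional on sponsor agreement. For a SUSAR, the same section has the system manager send the code directly to pharmacovigilance staff. Regulatory reporting therefore has a more direct route to the code than rescue has.

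**The case against.** The strongest defence is that withdrawal here mostly means leaving study treatment. Progression is itself a withdrawal criterion, so if withdrawal ended survival follow-up, hardly any OS could be observed. Sections 7, 8, 9 and 13.4.1 all look past it. The follow-up sentence in 4.4.3 can be read as follow-up of the emergency, alongside ordinary survival follow-up. Even read literally, it captures deaths from the emergency itself; only later deaths could be missed. All of this stands, and it is why the point is a contradiction to be resolved and not a demonstrated loss of data.

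A reader might infer more, in four ways that the documents do not support:
- That PFS and OS data are certainly lost. Loss arises only if a site follows 4.4.3, or 3.2.2, literally and ignores sections 7 and 9.
- That the rule breaks ITT. Section 13.1 keeps every randomised patient, and 4.4.3 says nothing about exclusion or censoring. Membership of the set, however, does not supply a missing date.
- That an OS HR of 0.70 would read about 0.65. That comes from deleting 12 of an assumed 154 arm 1 deaths (0.70 × 142/154 = 0.645). It takes 5% vs 0% with every such patient dying, and it keeps their person-time at risk. Censoring removes both, which gives the smaller shifts above.
- That Table S3 shows how unblinding differs by arm. Grade 3 or higher immune-related events were 16.7%, 8.2% and 6.9% (arm 1, arm 2, control). These are trial results, not planning inputs, and include events that would not call for unblinding. They make a difference by arm plausible but do not measure it.

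The sponsor's right to refuse has no counterpart elsewhere that softens it. That it delays care is an inference, since the protocol states no response time.

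**Conclusion.** The point holds as two contradictions. First, the withdrawal and follow-up rule in 4.4.3 cannot be squared with sections 7, 8 and 9. If applied literally, it could censor patients informatively and unequally between arms, with PFS less protected than OS. The likely size is small: an OS HR about 0.02 to 0.03 too favourable at assumed rates of 5% vs 0 to 1% with a threefold later hazard of death, about 0.05 at 10% vs 2%, and next to nothing when rates are low and equal. These figures rest on assumed rates, timing and hazards, none of which the documents supply.

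Second, making release of the code depend on sponsor agreement, with no time limit or override, is at odds with the condition that rescue depends on knowing the treatment. Both should be corrected. Neither shows that the primary results are biased.

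**What to change.** Reconcile 4.4.3, Handling after emergency unblinding, with sections 7, 8 and 9. State that emergency unblinding does not end scheduled tumour assessment or survival follow-up, and is not a reason for censoring in the ITT analysis. Make the AE-only wording of 3.2.2 consistent with this.

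Reconcile the process for emergency unblinding with its condition. Replace sponsor approval with access by the site in the randomisation system, and notify the sponsor afterwards without the allocation.

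The cost is an amendment to the wording and one setting in the randomisation system. The tumour assessments and survival contacts are already scheduled, so no visits are added.
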